### Sample size estimation

Sample size calculation of this study is based on the findings of a previous study on the implementation of an intervention aiming to enhance CRC screening uptake among African Americans, under which the difference in CRC screening uptake between the intervention and control groups at six-month follow up was compared [29]. The authors observed a difference of 16.2% in the proportion of intervention and control participants who had undergone screening. To reject the null hypothesis that no difference in screening uptake exists between the two groups at a 5% level of significance, both groups require 126 dyads to achieve a power of 80%. To reach an attrition rate of 20%, a total of 320 dyads shall be recruited, with 160 dyads in each group.

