### Design

This study will utilize a cluster randomized controlled trial design, which includes a wait-list control group.

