### Randomization

A cluster randomization approach will be utilized in this study. In previous community-based projects, we had identified ten districts in Hong Kong populated with a large number of South Asians. These districts will be randomized into either the intervention or wait-list control group, with five districts allocated to each group respectively. Partner organizations located in each district will be allocated to either group based on the outcome of group allocation of respective districts. Sealed and numbered envelopes will be used during group allocation to ensure concealment. To ensure successful recruitment of 320 dyad participants for the study, we aim to recruit 50–60 dyad participants in each district.

Randomization will be conducted by a research staff member independent from the research team so that outcome assessors and study investigators will be blinded to group allocation. However, owing to the use of a wait-list control group in this study, it will not be possible to blind the dyad participants.

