### Data analysis

Descriptive statistics will be used to report the demographic characteristics of participants in both groups. The baseline characteristics of the two groups will be compared by chi-square or independent t-tests as appropriate. The effectiveness of the intervention will be evaluated by comparing the proportion of younger family members who expressed willingness to encourage their older family members to take up FOBT, as well as their readiness to assist older family members in collecting a stool sample at T1 in both groups. The proportions of older family members who attended medical visit at T2 and reported to have undertaken FOBT at T3 in both groups will also be evaluated. Chi-squared test will be employed for the analysis of these parameters with an intention-to-treat approach. Generalised linear models on the baseline and T1 data will be used to compare the differential changes in two repeated outcome measures for younger family members across the two time points between the two groups, with adjustment for potential confounding variables. The generalised linear modelling will be performed through the Generalised Linear Models Procedure of IBM SPSS statistic v22, depending on the distributions of dependent variables. Descriptive statistics will be used to evaluate dyads’ satisfaction level of the intervention. All statistical tests will be two-sided, with a *p*-value less than 0.05 being considered statistically significant.

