## Discussion

CRC screening is an effective way to detect precancerous lesions in colon and rectum, which enables early CRC detection. This increases the availability of treatment options and likelihood of cancer cure, thereby reducing CRC mortality [31]. Increased utilization of CRC screening would also be likely to reduce the prevalence of CRC worldwide, and should therefore be encouraged. Nevertheless, as indicated above, South Asian ethnic minorities were found to exhibit a low uptake of cancer screening, primarily due to their inadequate knowledge on cancer prevention and cultural beliefs. Moreover, our previous study also revealed that only 10% of South Asians aged 50 or above had previously undergone CRC screening [14], implying that the older generation of South Asian ethnic minorities tend not to utilize CRC screening services available to them. As CRC risks were shown to increase with age [4], the development and implementation of interventions, primarily targeting older South Asian adults, effective in promoting CRC screening uptake would be of paramount importance. Since older South Asian older were found to often rely on their younger family members in the acquisition of health-related information [27], a family-based approach would be required in the development of intervention that aims to raise the awareness on the importance of CRC screening in CRC prevention among older South Asian older adults. Here, a CRC screening intervention that targets both the younger and older members of families is proposed to enhance its effectiveness in disseminating information on CRC prevention among older South Asian older and encouraging the utilization of CRC screening. To the best of our knowledge, this is the first study dedicated to assessing the effectiveness of a family-based intervention to increase CRC screening uptake among South Asian ethnic minorities within a Chinese community.

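### The 80% power claimed for 126 dyads per group makes no visible allowance for randomising ten districts, so it is unsupported for this cluster design

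*Protocol article*

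**What the plan says.** The Design section of the protocol article states: "This study will utilize a cluster randomized controlled trial design, which includes a wait-list control group". The Randomization section makes the district the unit: "These districts will be randomized into either the intervention or wait-list control group, with five districts allocated to each group respectively".

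The Sample size estimation section takes its effect from an earlier screening trial in another population: "The authors observed a difference of 16.2% in the proportion of intervention and control participants who had undergone screening". It tests "at a 5% level of significance", and the Data analysis section adds "All statistical tests will be two-sided". From this it concludes that "both groups require 126 dyads to achieve a power of 80" per cent. The last step is "To reach an attrition rate of 20%, a total of 320 dyads shall be recruited, with 160 dyads in each group".

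The section gives neither group's uptake proportion, and no ICC, design effect, number of districts or cluster size. The nearest figure for uptake is in the Discussion, where the authors' previous study is said to show that "only 10% of South Asians aged 50 or above had previously undergone CRC screening". It describes past screening and is not offered as a design input. The Randomization section aims for 50–60 dyad participants in each district.

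**The concern.** When whole districts are randomised, dyads in the same district share community organisations, family doctors and social networks, so their screening behaviour is likely to be correlated. Each dyad then adds less information than an independently randomised one. With only five districts per arm, the between-district variance also rests on few degrees of freedom. A sample size that allows for neither overstates power.

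Uptake is the outcome that sizes the trial. If its result is null, readers will take the published 80% as a sign that a 16-point effect would probably have been seen. If the real figure is appreciably lower, that reading is unsafe.

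**Working it through.** **Inputs from the article:** difference d = 0.162; two-sided 5%; 80% power; 126 per group; 160 per group recruited; 20% attrition; five districts per arm.

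**Assumptions, because the article gives no value:** ICC 0.01, 0.02 or 0.05; control uptake p as shown; equal district sizes.

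**1. Can 126 be reproduced?** For individual randomisation with unpooled variance, n = (1.960 + 0.842)² × [p(1−p) + (p+d)(1−p−d)] / d².
- p = 0.24: 7.849 × (0.1824 + 0.2404) / 0.02624 = 126.4.
- The pooled-variance version gives 126 at p of about 0.222–0.225.
- The continuity-corrected version gives 126.2 at p = 0.18.
- At p = 0.10 the three versions give about 85, 88 and 99.

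So 126 is an ordinary individual-randomisation result at a control uptake of about 18–24%. The pooled and continuity-corrected versions also reach it at high control rates (about 61% and 66%).

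**2. The step from 126 to 160.** 126 / 0.8 = 157.5, rounded up to 160. Attrition accounts for the whole step; nothing is added for clustering.

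**3. Cluster size and design effect.** Analysed per arm: 160 × 0.8 = 128. Per district: m = 128 / 5 = 25.6. Design effect DE = 1 + (m − 1) × ICC.

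| ICC | DE | Effective n per arm (128/DE) |
|---|---|---|
| 0.01 | 1.246 | 102.7 |
| 0.02 | 1.492 | 85.8 |
| 0.05 | 2.230 | 57.4 |

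**4. Power if 126 per arm means 80% under individual randomisation.** The standardised effect is λ = 2.802 × √[(128/126)/DE]. Normal power is Φ(λ − 1.960). The t version uses a noncentral t with 10 − 2 = 8 degrees of freedom and critical value 2.306.

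| ICC | λ | Normal | t, 8 df |
|---|---|---|---|
| 0 | 2.824 | 81% | 70% |
| 0.01 | 2.530 | 72% | 60% |
| 0.02 | 2.312 | 64% | 53% |
| 0.05 | 1.891 | 47% | 38% |

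By normal approximation, 80% is kept only if ICC ≤ (128/126 − 1)/24.6 ≈ 0.0006. With no attrition at all (160 per arm, 32 per district), it is kept up to (160/126 − 1)/31 ≈ 0.009.

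**5. Power if control uptake were 10%** (26.2% with intervention), 128 per arm.

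| ICC | Normal (pooled) | t, 8 df |
|---|---|---|
| 0.01 | 86% | 77% |
| 0.02 | 79% | 70% |
| 0.05 | 62% | 53% |

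At this control rate 126 per group would give about 92% under individual randomisation, so this scenario does not match the article's own pairing of 126 with 80%.

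**6. Difference detectable with 80% power** (128 per arm, t on 8 df, control uptake 10–24%): about 17–21 points at ICC 0.01, 19–23 at 0.02 and 24–28 at 0.05, against the planned 16.2.

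**7. Does the district target change this?** Ten districts of 50–60 dyads make 500–600, whereas 320 / 10 = 32. If 50–60 were recruited and 20% lost, m = 40–48. On 8 df and over control uptake of 10–24%, power would be about 75–92% at ICC 0.01 and 44–62% at ICC 0.05.

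**The case against.** The strongest objection is that no single power figure follows from the article. ICC, control rate and reference distribution are all supplied from outside, and other reasonable choices move the answer: 86% at 10% control uptake, ICC 0.01 and a normal approximation; 81% on 8 df at 10% and ICC 0.005; 27–33% at ICC 0.10 on the calibrated basis. This stands. A reader might infer that the trial simply has 38–77% power, but the documents do not support that. The range depends on assumed inputs, and it joins two incompatible scenarios: the lower end uses a control rate at which 126 does give 80%, the upper end one at which about 85–99 per group would suffice.

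A reader might also infer that 126 is proven to be an individual-randomisation figure. Without the control rate this is a strong inference and no more. At 10% control uptake, 126 would leave room for a design effect of about 1.3–1.5 (126/99 to 126/85), though the section does not say that any was intended.

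The 8 degrees of freedom are not part of the planned chi-squared test, and they account for a good part of the loss: 81% becomes 70% even at ICC 0. That is why the normal-approximation figures are given beside them; on the calibrated basis those also fall below 80% at every ICC from 0.01 to 0.05.

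Finally, larger districts would help if the ICC is small. But 50–60 dyads per district contradicts the stated total of 320, and at ICC 0.05 it still does not restore 80%.

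The arithmetic from 126 to 160 is correct. The fault is an omission in the design calculation.

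**Conclusion.** The concern holds in limited form. The article randomises ten districts, yet its sample size passes from a 16.2-point difference to 126 and then to 160 per group with attrition as the only allowance. The 80% power is therefore unsupported as stated.

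The size of the shortfall is illustrative. On the article's own pairing of 126 with 80%, and for ICCs of 0.01–0.05, power is about 72–47% by normal approximation or 60–38% on 8 degrees of freedom. With a 10% control uptake it is 77–53% on 8 degrees of freedom. These figures assume 128 dyads analysed per arm in five equal districts. An ICC close to zero, a low control uptake or more dyads per district would narrow or close the gap. The missing clustering allowance does not depend on any of these assumptions.

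**What to change.** Keep 320 dyads and revise the Sample size estimation section so that it:
- states the control and intervention proportions behind the 16.2 points;
- gives an ICC range with its basis (0.01–0.05 would serve as an illustration);
- shows the design effect 1 + (m − 1) × ICC and the 8 between-district degrees of freedom;
- uses a cluster size m reconciled with the Randomization section, since 50–60 dyads per district and 320 in total cannot both hold;
- reports the resulting power for 16.2 points and the difference detectable with 80% power;
- withdraws the unqualified claim that 126 dyads per group give 80% power.

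The cost is rewording and a short recalculation. The downside is that the stated power becomes less favourable. The change describes the trial's power correctly; it does not raise it.

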### Subject recruitment

Recruitment of South Asian dyads will be carried out at partner organizations within local communities in Hong Kong. Prior to the implementation of intervention, our research staff will approach potential partner organizations to seek their support in subject recruitment. These organizations will be asked to distribute a subject recruitment notice amongst their South Asian members in form of posters and social media posts. Persons-in-charge of these organizations will also be invited to contact their members for taking part in the study. Permissions to recruit potential dyads during the social activities under partner organizations will also be sought. Potential dyads interested in joining the study will be screened for eligibility before enrolment.

### Randomization

A cluster randomization approach will be utilized in this study. In previous community-based projects, we had identified ten districts in Hong Kong populated with a large number of South Asians. These districts will be randomized into either the intervention or wait-list control group, with five districts allocated to each group respectively. Partner organizations located in each district will be allocated to either group based on the outcome of group allocation of respective districts. Sealed and numbered envelopes will be used during group allocation to ensure concealment. To ensure successful recruitment of 320 dyad participants for the study, we aim to recruit 50–60 dyad participants in each district.

Randomization will be conducted by a research staff member independent from the research team so that outcome assessors and study investigators will be blinded to group allocation. However, owing to the use of a wait-list control group in this study, it will not be possible to blind the dyad participants.

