### Participants

A total of 320 dyads of older South Asian adults and their younger family members will be recruited for the study. The inclusion criteria for older adults include 1) having a South Asian origin (either Indian, Pakistani or Nepali), 2) aged between 50 and 75, 3) having a younger family member or relative aged between 18 and 49, and 4) residing in Hong Kong during subject recruitment. Those participated in our previous community-based project titled ‘A community health worker-led multimedia intervention to increase cervical cancer screening uptake among South Asian women: A randomized controlled trial’ will be excluded.

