#### Maintenance

The ‘Maintenance’ of the intervention will be assessed by the level of willingness for persons-in-charge of partner organizations to continue implementing our intervention at their centers after project completion. An author- developed questionnaire with a five-point rating scale will be used for the assessment.

Demographic data, including age, ethnic group, number of people in the household, monthly household income, years of formal education, marital status, employment status, number of years’ residence in Hong Kong, family history of cancer, health insurance status, acculturation and relationship of the dyad members, will also be collected by means of an author-developed questionnaire.

All questionnaires used in outcome measurement will first be developed in English and subsequently translated into Urdu, Nepali and Punjabi by our research staff member of a South Asian origin. Back-translation will be conducted to ensure content and semantic equivalence in the translated questionnaires. A panel consisting of individuals fluent in Urdu, Nepali or Punjabi, and those involved in educating South Asians on health promotion and cancer prevention will be invited to proofread the Urdu, Nepali and Punjabi versions of the questionnaire to ensure the validity of the contents.

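### The doctor-visit and FOBT outcomes get an unadjusted chi-squared test, although only ten districts are randomised and ethnic group and age are collected at baseline

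*Protocol article*

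**What the plan says.** **Allocation.** The Randomization section says the team, in earlier projects, "we had identified ten districts in Hong Kong populated with a large number of South Asians", and continues: "These districts will be randomized into either the intervention or wait-list control group, with five districts allocated to each group respectively". Sealed, numbered envelopes are described. Stratification, matching or another balancing factor is not.

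**Who is enrolled.** Older adults qualify by "having a South Asian origin (either Indian, Pakistani or Nepali" (Participants), so three ethnic groups enter the trial.

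**What is collected.** Under Outcome measures (end of the Maintenance subsection): "Demographic data, including age, ethnic group, number of people in the household", followed by income, education, insurance, acculturation and other items. The Data collection section places this at T0.

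**How the uptake outcomes are analysed.** The Data analysis section lists the younger members' willingness and readiness proportions at T1 and then "The proportions of older family members who attended medical visit at T2 and reported to have undertaken FOBT at T3 in both groups". For all of these: "Chi-squared test will be employed for the analysis of these parameters with an intention-to-treat approach".

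**Where adjustment appears.** Only in the next sentence, on generalised linear models for "differential changes in two repeated outcome measures for younger family members across the two time points between the two groups". Those are the baseline and T1 ratings of the younger members.

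**The concern.** A chi-squared test of two proportions carries no covariates and no district term. The plan therefore treats confounding as worth handling for the younger members' ratings. It does not do so for screening uptake, the behaviour on which the sample size is built.

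Individual randomisation of 320 dyads would make a large imbalance in ethnic group unlikely. Randomising ten districts does not, if the groups tend to live in different districts. A realised imbalance in a covariate that predicts uptake moves the observed difference up or down, and the planned test has no means of removing that part. The planned baseline comparisons might reveal such an imbalance, but nothing in the FOBT analysis uses their result. Choosing covariates only after seeing it would be a post hoc decision.

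**Working it through.** **1. The plan's own figures.** The Sample size section gives a difference of 16.2 points, 5% significance, 80% power, 126 dyads per arm, and 320 in total after 20% attrition. The control rate is not stated, so 126 can be checked only conditionally. The formula is n = [1.96·√(2·p̄·q̄) + 0.8416·√(p₁q₁ + p₂q₂)]² / 0.162². A control rate of 21–23% gives n = 123–127 without continuity correction (17–18% gives 124–127 with it). Attrition: 126/0.8 = 157.5, so 158, rounded to 160 per arm. The point below does not depend on 126 and uses only the 16.2 points as a yardstick.

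**2. How often a 5/5 split of ten districts is uneven.** There are C(10,5) = 252 allocations. If K districts share a feature, the number that put *a* of them in the intervention arm is C(K,a)·C(10−K, 5−a).
- K = 4: 2:2 in 6×20 = 120 (48%); 3:1 either way in 2×4×15 = 120 (48%); 4:0 either way in 2×1×6 = 12 (5%). So 132/252 = 52% are 3:1 or worse.
- K = 2: both in one arm in 2×C(8,3) = 112 (44%).

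These counts are exact, but which K applies is unknown.

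**3. What an uneven split does to the FOBT difference.** Assumptions, none of them in the article: equal district sizes; K districts in which one ethnic group has share *h*, and the rest with share *l*; uptake differing by *g* points between that group and the others. With *a* and *b* of the K districts in the two arms,

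shift = g × (h − l) × (a − b)/5.

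Example: K = 4, h = 80%, l = 10%, g = 20. A 3:1 split gives 20 × 0.70 × 2/5 = 5.6 points, and a 4:0 split gives 20 × 0.70 × 4/5 = 11.2 points. A 2:2 split gives 0.

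RMS shift over all 252 allocations, in percentage points:

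| K | h / l | g = 10 | g = 20 |
|---|---|---|---|
| 3 | 80% / 10% | 2.1 | 4.3 |
| 3 | 60% / 20% | 1.2 | 2.4 |
| 3 | 50% / 30% | 0.6 | 1.2 |
| 4 | 80% / 10% | 2.3 | 4.6 |
| 4 | 60% / 20% | 1.3 | 2.6 |
| 4 | 50% / 30% | 0.7 | 1.3 |
| 5 | 80% / 10% | 2.3 | 4.7 |
| 5 | 60% / 20% | 1.3 | 2.7 |
| 5 | 50% / 30% | 0.7 | 1.3 |

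For instance, K = 5 at 80%/10% gives share differences of 0.14 (200 allocations), 0.42 (50) and 0.70 (2). Then √[(200×0.14² + 50×0.42² + 2×0.70²)/252] = √(13.72/252) = 0.233, and 20 × 0.233 = 4.7 points.

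**4. Scale.** With 160 per arm and rates of 22% and 38.2%, the individual-level standard error of the difference is √[(0.22×0.78 + 0.382×0.618)/160] = 0.050, about 5 points. Adding the RMS shift in quadrature gives √(5.05² + 0.6²) = 5.1 points at the low end and √(5.05² + 4.7²) = 6.9 at the high end. The added error is thus between negligible and nearly as large as the individual-level sampling error.

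**The case against.** **The effect may be small.** This stands. The article gives no ethnic mix by district and no uptake by ethnic group. In the four-district example 48% of allocations are exactly balanced. Even a 3:1 split shifts the difference by 5.6 points under the strongest assumptions for that case, only slightly more than one individual-level standard error.

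**Randomisation already protects the estimate.** This also stands, as far as it goes. Over repeated allocations the unadjusted difference is not biased. Imbalance adds between-district variance, which a valid cluster analysis would carry in its standard error. The planned chi-squared test does not carry it. That is a related but separate defect. A cluster-aware test would cure it without recovering the precision that covariates offer.

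**The abstract names generalised linear models for the data in general.** The Data analysis section is the specific text. It assigns the T2 and T3 proportions to chi-squared and limits the models to the younger members' two repeated measures.

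Three stronger readings are tempting and not supported:
- *The allocation is unrestricted.* The article never says so. It is a condensed account that describes no balancing factor, and a fuller protocol might.
- *Ethnic group is a known predictor of uptake in this trial.* The article compares ethnic minorities with the general population. It reports 10% prior screening among South Asians aged 50 or above and does not break this down by group.
- *The T1 proportions are protected by adjustment.* They too go to the chi-squared test. Only the baseline-to-T1 change is adjusted.

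**Conclusion.** The point holds as an avoidable loss of precision in the analysis of the T2 and T3 outcomes. The unadjusted test is stated outright, the covariates are already planned for collection, and ten randomised units make chance imbalance a practical possibility. The RMS shift is about 0.6 to 4.7 points against the 16.2-point planning difference. That range rests wholly on assumed district mixes and assumed uptake gaps of 10 or 20 points, with equal district sizes.

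A reader might infer that the trial's effect estimate is biased, or that the districts ought to be re-allocated under a balance constraint. Neither follows. The estimator is unbiased over allocations. Constrained allocation is a design preference, and it probably comes too late given the 1 September 2018 start under Trial status. Balancing on expected dyad numbers would add little, because Randomization sets the same recruitment target for every district.

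**What to change.** In the Data analysis section, replace the chi-squared test for the T2 visit and T3 FOBT proportions with one prespecified model for each that:
- accounts for district as the randomised unit, with a small-sample correction suited to ten clusters;
- adjusts for a short set of T0 covariates named in advance, such as ethnic group and age of the older adult;
- reports the adjusted difference in proportions with its confidence interval, so that it can be read against the 16.2-point planning difference.

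The covariate list should be fixed before outcome data are seen and should not depend on the baseline significance tests. It should stay short and consist of individual-level variables, because ten clusters leave little room for district-level terms.

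The cost is a change of analysis wording and slightly more analysis work. No new data, visits or participants are needed, and the allocation of districts is left as it is.
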